In this trial, a validated wrist specific PRWE-score is used as the primary outcome measure. Just recently Wallenkamp and coworkers published a report, where minimal clinically important difference in PRWE was set at 11 points with SD of 14 [37]. Based on power calculations (Cl 95%, power 0.95, SD 14) required sample size per group is 40 patients. Assuming 30% of drop-out due to possible surgical interventions during cast treatment, group size would be 52 per group (total 104). In case of patient cross-over, patients will be analyzed according to the intention-to-treat principle.

- 1. **ANALYSIS OF THE MATERIAL**

Each patient will get an initial trial identification number (TIN) which is matched with actual patient identification (ID). **The matching key is stored in study nurse’s office in Tampere University Hospital. Patients are handled only with TIN during follow-up period and analyzing the of the material. Results are given only in general level with mean values thus individual patient’s information is not able to be extracted. The electronical registry contains x-rays and it is located in hospital’s secure server. The research data will be deleted 15 years after the end of the study.**

- 1. **STATISTICAL ANALYSIS**

Continuous skewed variables between the groups were compared by the Mann-Whitney *U* test and t-test is used when variables are unskewed. Results are presented with 95% confidence intervals. Two-way-tables with the chi-square test will be used for dichotomous variables. In subgroup analysis the effect of age, sex, fracture group, smoking, and other diseases will be evaluated against the scores and overall quality of life after fracture.

Analysis of covariance will be used to assess the effect of pain catastrophizing score on the outcome of cast treatment. PRWE will be used as a dependent variable, cast as independent and pain catastrophizing score as covariate.

The effect of cast position and PRWE is investigated also in the multivariate manner. Multivariable analysis is performed with linear regression analysis since the outcome variable PRWE is normally distributed. Main variable of interest included is the cast and age, sex, fracture group, smoking and other diseases are used as confounding variables.

- 1. **ETHICAL ISSUES**

The ethical approval of this study is applied with this research plan.

1. **IMPLEMENTATION**
   1. **CONTINGENCY PLAN**

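### The 30% drop-out allowance is added by multiplying 40 by 1.3 instead of dividing by 0.7, so 52 per group gives about 91% power after the stated loss, not 95%

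*Protocol*

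**What the plan says.** The Power analysis section of the protocol bases the sample size on the PRWE score. It takes from a published report that the "minimal clinically important difference in PRWE was set at 11 points with SD of 14". It continues: "Based on power calculations (Cl 95%, power 0.95, SD 14) required sample size per group is 40 patients". The allowance for loss follows at once: "Assuming 30% of drop-out due to possible surgical interventions during cast treatment, group size would be 52 per group (total 104" patients). The last sentence of the paragraph says that patients who cross over are analysed by intention to treat.

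The Contingency plan carries the result forward as a need to recruit more than 100 patients. Under Study design the primary outcome is PRWE at one and two years, and under Follow-up both of those assessments are postal. No other part of the protocol corrects or recalculates the figure.

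**The concern.** An allowance for loss has to be sized so that the number required is still there after the loss. Multiplying by 1 + d, where d is the proportion lost, does not do this. The loss is taken from the enlarged group, so the divisor should be 1 − d. At small d the two nearly agree; at 30% they differ by 6 patients per group (52 against 58).

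The paragraph therefore promises 95% power on a group size that its own drop-out assumption does not support. The statement concerns the primary comparison, and a trial report would be likely to repeat it. A reader who sees 40, 30% and 52 together can find the slip in one line.

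**Working it through.** **Inputs, all from the Power analysis section.** Difference 11 points; SD 14; confidence level 95%; power 0.95; 40 evaluable per group; loss 30%; 52 randomised per group, with equal groups. Sidedness is not stated in words. I read two-sided 5% from "Cl 95%, power 0.95, SD 14" and from the Statistical analysis section: "Results are presented with 95% confidence intervals".

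**1. The plan's own step.** 40 × (1 + 0.30) = 52 per group, 104 in total. This reproduces the protocol's figure exactly.

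**2. The same step done by division.** 40 / (1 − 0.30) = 57.1, so 58 per group, 116 in total.

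**3. What 52 leaves.** 52 × 0.70 = 36.4, so about 36 evaluable per group. The largest loss that still leaves 40 is 1 − 40/52 = 23.1%.

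**4. Power after the stated loss.** By the normal approximation, power = Φ[(Δ/σ)·√(n/2) − 1.960].

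- n = 36: (11/14) × √18 = 3.334; 3.334 − 1.960 = 1.374; power 0.915.
- n = 40: (11/14) × √20 = 3.514; 3.514 − 1.960 = 1.554; power 0.940.

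| Evaluable per group | Normal | t-test (noncentral t) |
|---|---|---|
| 36 | 0.915 | 0.908 |
| 40 | 0.940 | 0.935 |
| 43 | 0.954 | 0.950 (0.9496) |
| 44 | 0.958 | 0.954 |
| 52 | 0.980 | 0.978 |

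By the t-test, the type II error at 36 is 1 − 0.908 = 9.2%, against the planned 5%.

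**5. The starting figure of 40.** n = 2(1.960 + 1.645)²(14/11)² = 42.1, so 43 per group. The t-test gives 43.08, so 44. The stated 40 is 3 to 4 short, which costs 1 to 1.5 points of power. Repairing this step as well as the drop-out step would need 43/0.7 = 61.4, so 62 per group (124), or 44/0.7 = 62.9, so 63 per group (126).

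**6. Loss for other reasons.** The protocol ties its 30% to surgery alone and gives no figure for death or questionnaires not returned. Purely as an assumption, a further 10% loss leaves 52 × 0.7 × 0.9 = 32.8 per group and t-test power 0.88. A further 20% leaves 52 × 0.7 × 0.8 = 29.1 and power 0.84.

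**The case against.** **Power is still above 90%.** This stands. A reader might infer that the trial is seriously underpowered; the protocol's own inputs do not show that. The paragraph states a power that the design does not have, but the design still works at the stated difference and SD. That limits the severity.

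**The 40 may come from an unrounded input.** A difference of about 11.4 would give 40 at 95% power, and 11.4 rounds to 11. The protocol prints only 11, so this is conjecture, but it is a fair reason to treat the shortfall at 40 as secondary. It does not rescue the drop-out step: with 11.4 points, 36 per group gives about 93%.

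**The test might be one-sided.** At one-sided 5%, 36 per group gives 95.1% power, and 36/0.7 = 51.4 rounds up to 52. The end figure would then be right, but the protocol states 40, not 36, as the number required. A one-sided calculation does not yield 40, and the 95% confidence level points to a two-sided test.

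**Any postal non-response would more than double the type II error.** A reader might infer this, but it goes too far. The error is about 9% at 36 per group and passes 10% only at about 35, so some further loss is needed first. The protocol gives no rate for such loss.

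**Keeping operated patients would restore 95–96% power.** A reader might infer this from the intention-to-treat sentence: with 10–15% other loss (assumed), 52 per group gives 0.964–0.955. But that takes the full 11 points as intact when up to 30% of each arm has had surgery. If operated patients showed no effect of cast position (an assumption, for illustration), the difference would be 0.7 × 11 = 7.7 points. Power would then be about 0.75–0.72 with the same 10–15% loss. The protocol attaches intention to treat to cross-over and counts surgery as drop-out, so it supports no such restatement.

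**Conclusion.** The drop-out step is wrong as written, with moderate severity. The allowance in the protocol covers a 23% loss, not the 30% it names, and the power that follows from its own assumptions is about 4 points below the one it states. The arithmetic of the drop-out step depends on no outside source. The power figure rests on a difference of 11, SD 14, equal groups, a two-sided 5% test (inferred) and the full 30% being lost from the analysis.

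The shortfall at 40 per group is real but small and should not carry the point. The effect of death and non-response has a known direction and an unknown size.

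**What to change.** Replace the drop-out sentence in the Power analysis section with wording such as:

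> 52 patients are randomised per group (104 in total). With 30% loss, about 36 per group are evaluable, which gives about 91% power to detect a difference of 11 points (SD 14, two-sided 5%).

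Add that the 30% refers to surgery only, and that death or unreturned questionnaires at one and two years would lower power further; the range in step 6 can serve as an example if labelled as assumed. State the sidedness in words. Correct the starting figure too, by giving 93.5–94% as the power at 40 or 43–44 as the number for 95%.

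Do not claim 95–96% power on the ground that operated patients stay in the analysis, unless the assumed difference is first reduced for dilution by surgery.

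The cost is one paragraph of wording and a slightly less favourable power statement. Enrolment rises only if the sponsor prefers to hold a target: 116 in total to keep 40 evaluable per group, or 124–126 to deliver 95% power after 30% loss.

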Other methods of immobilization are functional bracing, immobilization wrist in neutral and slightly extended position as well as in pronation or in supination [13-16]. Cochrane database review regarding conservative treatment of DRF in adults concluded that there is insufficient evidence from randomised trials to determine which method of conservative treatment is the most appropriate when treating most common types of adult DRF [24].

It has been suggested that fracture stability during conservative treatment is not related to cast or immobilization position properties but merely ‘inherent’ characteristics of fracture as well as the patient [4,9-12,24]. Current evidence also indicates that the functional outcome of DRF in elderly people (>65) is not related to anatomic alignment of the fracture [25-30]. Weak evidence supports neutral (radius-metacarpal line 0°) or functional (radius-metacarpal line 20° of extension) reduction [17,18,24]. This practice has been adopted by several countries in their guidelines of DRF treatment. However, the evidence supporting this position is scarce and there are no high quality RCT studies in the English language literature comparing commonly used slight flexion-ulnar deviation -position and functional position.

Functional outome in DRF patients can be affected other than fracture alignment or other fracture spesific factors as well. Pain catastrophizing and fear to use injured limb are shown to increase disability, increased pain and muscle weakness in upper extremity and DRF patients [31-34]. The severity of acute pain, catastrophic thinking and trauma related anxiety has been shown to associate with finger stiffness after DRF [35]. Pain catastrophizing scale (PCS) is one of the most widely used measure of catastrophic thinking related to pain [36]. PCS has been translated into several languages and is widely incorporated in the assessment protocol of pain clinics and rehabilitation centres. However, pain catastophizing as a predictor of funtional outcome has not been previously studied with consevartively treated DRF in elderly people.

1. **OBJECTIVES**

The aims of the present pragmatic collaboration study on the conservative treatment of DRFs are:

1. to compare two cast position (volar flexion, ulnar deviation cast position and functional cast position) by means of functional outcome measured with patient rated wrist evaluation (PRWE) score in persons aged 65 or more.

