2. to compare pain, disability, quality of life, grip strength, number of complications and cast changes after DRF treated with these two different cast positions
3. to assess the effect of PCS on the functional outcome of conservatively treated DRFs and the possible interaction between PCS and the functional outcome of DRF treatment with two different cast positions
4. **PRIMARY HYPOTHESES**

Our primary null hypotheses are as follows:

1. functional cast position gives similar functional outcome than currently used flexion-ulnar deviation cast position
2. functional cast position yields to similar results to currently used flexion-ulnar deviation cast position with regard to quality of life and grip strength and also with lower rates of complications and number of cast changes during immobilization when treating DRFs.
3. high PCS does not have an interaction with functional outcome on the patient rated wrist evaluation (PRWE) scale after adjusting for cast position used in the conservative treatment
4. **STUDY DESIGN**

The study is a pragmatic, prospective, randomized, controlled, multi-center trial. It is aimed to compare two different positions of a cast. The two cast positions compared are flexion-ulnar deviation position (widely used in Finland) and functional position used in other Nordic countries.

Primary outcome in this study is PRWE score measured after one and two years. Secondary outcomes measured are disability [Quick-DASH (disabilities of the arm, shoulder and arm)], pain in visual analogue scale (VAS), PCS, quality of life (15-D), complications and number of surgical interventions and cast changes. Subgroup analysis will be performed to find out patient specific features indicating good or worse outcome. PCS is used to assess the presence of possible mental susceptibility possibly influencing to the functional outcome.

1. **RESEARCH METHODS AND MATERIAL**
   1. **PATIENT SELECTION**

The eligible study population will consist of all consecutively (aged 65 or more) treated patients with a DRF identified in the public or referral emergency departments of participating hospitals.

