**3 m Follow-Up**

GP´s visit and x-ray prior to cast removal

Mailed questionnaires, no physician´s visit

 PRWE, QuickDash, VAS, 15-D, PCS

Physician´s visit at study hospital, x-ray

 PRWE, QuickDash, VAS, PCS, 15-D ROM, grip

Excluded

Direct operative treatment

Refuse to participate the study

Open fracture more than Gustilo 1 gradus

Age 64 or less

Chauffeure’s or Barton´s fracture

Smith´s fracture (volar angulation of the fracture)

Does not understand written and spoken guidance in local languages

Pathological fracture or previous fracture in the same wrist, antebrachium or elbow

Pathological fracture or previous fracture in the same upper extremity

Allocation to functional cast and PCS

GP´s visit + x-ray if seen necessary by the physician on-call

Cast immobilization time will be 5 weeks according to current guidelines in Finland. The final physician’s visit will be at the time of the cast removal. All patients have an x-ray prior to cast removal. After cast removal, the decision to refer patient for physiotherapist will be left to discretion of the treating physician.

After three months the patient will visit orthopedic outpatient clinic in the hospital where the treatment was initially started (Table). This visit is part of the study protocol. During the visit a direct lateral and anteroposterior radiographs will be taken. PRWE, PCS, Quick-DASH, 15-D and pain in VAS will be assessed. The number of cast changes during treatment is queried from the patient and the number of changes is recorded.

The 1- and 2-year **follow-ups are executed with postal questionnaires in order to reduce patients’ discomfort and aiming to as easy-as possible handling of the follow-up data. Controls include** PRWE, VAS (for level of pain), PCS, Quick-DASH and 15-D.

At the 1 and 2 year follow-up complications will be recorded from patient records.

|  | **Medical history** | **Radiograph** | **PRWE** | **PCS** | **Pain** | **Grip** | **Quick-DASH** | **15-D** | **VAS** |
| --- | --- | --- | --- | --- | --- | --- | --- | --- | --- |
| **Baseline** | x | X |  | x |  |  |  |  |  |
| **1-2 weeks** | (x) | (x) |  |  |  |  |  |  |  |
| **5-6 weeks** | (x) | X |  |  |  |  |  |  |  |
| **3 months** | x | X | x | x | x | x | x | x | x |
| **1 year** |  |  | x | x | x |  | x | x | x |
| **2 years** |  |  | x | x | x |  | x | x | x |

(x) = taken if required by the treating GP

**Table**: Assessments and procedures of the trial.

- 1. **POWER ANALYSIS**

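### The only drop-out allowance is for surgery during casting; nothing covers death or unreturned postal forms, so 52 per group does not secure the stated 95% power on the protocol's own reading

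*Protocol*

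**What the plan says.** Power analysis takes its inputs from a published study: "minimal clinically important difference in PRWE was set at 11 points with SD of 14". It continues: "Based on power calculations (Cl 95%, power 0.95, SD 14) required sample size per group is 40 patients". The next sentence inflates 40 to 52 per group (104 in total), and the reason is "Assuming 30% of drop-out due to possible surgical interventions during cast treatment". The sentence after that says that patients who cross over are analysed by intention to treat.

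The Study design section states: "Primary outcome in this study is PRWE score measured after one and two years". The first objective concerns the "patient rated wrist evaluation (PRWE) score in persons aged 65 or more". Under Follow-up, the one- and two-year contacts "are executed with postal questionnaires in order to reduce" patient burden, and the flow chart shows no physician's visit at those times. A PRWE is also taken at 3 months, at a hospital visit that belongs to the study protocol.

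For the comparison of casts, Statistical analysis names the Mann-Whitney test for skewed variables, while the "t-test is used when variables are unskewed". It adds an analysis of covariance with the pain catastrophizing score and a multivariable linear regression. None of these uses the 3-month PRWE to inform the later time points.

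**The concern.** The allowance covers an event in the five weeks of casting, whereas the primary outcome is read one and two years later from forms returned by post. In people aged 65 or more, some will die and some will not reply. The protocol counts neither. If the 30% is used up by surgery, as its wording says, nothing is left for these losses and the trial has less power than it claims.

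The intention-to-treat sentence points the other way. If an operated patient stays in the analysis, surgery does not by itself remove a PRWE form, and the extra patients are free to absorb non-return. The protocol does not say which of the two it means, so a reader cannot tell what power 52 per group provides.

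**Working it through.** **Inputs.** Difference 11, SD 14, power 0.95, 40 per group before and 52 after inflation, and 30% loss, all from Power analysis. Alpha is 0.05 from the 95% confidence level. Two-sided testing is an assumption, because sidedness is not stated. The protocol gives no rate of death or non-return, so a further 10, 15 or 20% is assumed.

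**1. The stated base of 40.** The normal formula is n = 2 × [14 × (1.960 + 1.645) / 11]² = 42.1, so 43 per group. The t-test needs 44. The stated 40 is not reproduced. It gives 93.5% power by the t-test (94.0% by the normal approximation).

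**2. The inflation.** 40 × 1.3 = 52 reproduces the stated figure. To leave 40 after 30% loss, the calculation is 40 / 0.7 = 57.1, so 58 per group. With 52, the number left is 52 × 0.7 = 36.4.

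**3. Operated patients lost, as the allowance is worded.** Evaluable per group = 52 × 0.7 × (1 − m), where m is the further loss among the rest. Power is by the two-sided t-test.

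| Further loss m | Total loss | Left per group | Power | Cost of m alone |
|---|---|---|---|---|
| 0% | 30% | 36.4 | 91.1% | – |
| 10% | 37% | 32.8 | 87.9% | 3.2 points |
| 15% | 40.5% | 30.9 | 86.0% | 5.1 points |
| 20% | 44% | 29.1 | 83.8% | 7.3 points |

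The step from 95% to 91.1% (3.9 points) has nothing to do with death or non-return. About 1.5 points come from the low base (95 to 93.5) and about 2.4 from multiplying instead of dividing (93.5 to 91.1).

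**4. Operated patients followed, analysed and keeping the full 11-point effect.** Evaluable per group = 52 × (1 − m).

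| Loss m | Left per group | Power |
|---|---|---|
| 0% | 52 | 97.8% |
| 10% | 46.8 | 96.4% |
| 15% | 44.2 | 95.5% |
| 20% | 41.6 | 94.3% |

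On this reading 95% holds up to about 15% loss if 44 whole patients are required (1 − 44/52 = 15.4%), or about 17% without rounding.

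**5. What the 3-month score could add.** Take 3-month PRWE as complete, 15% lost at one year and 20% at two years, with equal correlation between all times. At an assumed correlation of 0.6, 0.7 or 0.8, a joint model gives an effective 45.1, 46.4 or 47.9 per group at two years, against 41.6 returned forms. Of the 52 − 41.6 = 10.4 lost, this recovers (45.1 − 41.6)/10.4 = 34% to (47.9 − 41.6)/10.4 = 61%.

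**6. Bias, as illustration only.** Suppose non-return rises with 3-month PRWE by 1 on the log-odds scale per SD in one arm and not at all in the other, with correlation 0.6 and about 20–24% loss. A comparison of returned forms is then off by up to about 1.7 points (1.7/11 = 15% of the target). With slopes of 0.5 and 1 it is off by no more than about 0.9 points (8%). Nothing in the protocol suggests that either pattern will occur.

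**The case against.** The best defence is the intention-to-treat sentence. If operated patients still receive and return the form, 52 per group has power to spare, and step 4 shows about 95% up to 15–17% loss. That stands as arithmetic. It requires operated patients to keep the whole cast effect, and it requires the 30% to mean something other than what the protocol says. The same 12 patients per group cannot replace both those lost to surgery and those who do not reply.

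The second defence is that much of the shortfall from 95% has other causes. This also stands. At 10% further loss, 3.9 of the 7.1 missing points come from the base and the inflation, and only 3.2 from non-return. The size of this point is therefore 3 to 7 points, on assumed rates.

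A reader might go further and infer that the protocol commits to discarding everyone who does not return a form, and that the result will be biased. The document does not support this. The named tests use only observed values when run alone, but no complete-case rule is stated. Handling of missing data may be set out in a statistical analysis plan that is not shown, and its absence from the protocol is not an error. The bias figures show what could happen under strongly one-sided non-return, not what this plan produces.

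**Conclusion.** The point holds as one about the sample-size statement. The protocol makes one allowance, ties it to surgery, and makes none for death or unreturned forms, although the primary outcome depends on those forms. If operated patients are lost, power is 91% before any other loss and 84–88% after an assumed further 10–20%. If they are kept with the full effect, it is 94–96% at the same losses. The claim of 95% is thus met only on the more favourable reading and only up to about 15–17% loss.

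The consequence is moderate. Power stays above 80% in every case shown, so the trial is not undermined, but the stated figure should be corrected. The result rests on a two-sided t-test, on the protocol's own 11 and 14 points, and on loss rates that the document does not supply. The mixed model is a better use of data already collected. It is offered as an improvement, not as the correction of a stated error.

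**What to change.** **Power analysis.** Define the allowance as loss of the PRWE form at one and two years from any cause, and list surgery, death and non-return separately. State whether operated patients continue to be sent the form and are analysed, so that the allowance and the intention-to-treat sentence agree. Then restate the power for 52 per group at the assumed total loss, using figures such as those in the two tables above. No patients need be added. The cost is a few sentences and a less favourable stated power.

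**Statistical analysis (recommended improvement).** Take the cast difference at one and two years from one mixed model of PRWE at 3 months, 1 year and 2 years, with cast, time and cast-by-time. Patients with a 3-month score but no returned form then still contribute. The cost is slightly more analysis work and reliance on a missing-at-random assumption: that loss is explained by the scores already observed. The data cannot confirm this, although it asks less than treating returned forms as representative.

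### The named tests use one visit at a time, so a patient's earlier PRWE scores do not inform the 1- or 2-year comparison when that visit's postal form is missing

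*Protocol*

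**What the plan says.** Study design sets the endpoint: "Primary outcome in this study is PRWE score measured after one and two years". Under Follow-up, the 3-month hospital visit is part of the study, and there "PRWE, PCS, Quick-DASH, 15-D and pain in VAS will be assessed". The later "follow-ups are executed with postal questionnaires" and collect the same instruments. The assessment table confirms three PRWE readings per patient and none at baseline.

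Statistical analysis names these methods for the scores:

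- "Continuous skewed variables between the groups were compared by the Mann-Whitney" test, and the "t-test is used when variables are unskewed".
- An ANCOVA: "PRWE will be used as a dependent variable, cast as independent and pain catastrophizing score as covariate".
- A regression: "Multivariable analysis is performed with linear regression analysis since the outcome variable PRWE is normally distributed". Its covariates are age, sex, fracture group, smoking and other diseases.

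No method includes visit, a within-patient term or an earlier PRWE score. The section does not say which visit each test uses and has no rule for missing questionnaires. Intention-to-treat appears in Power analysis, for cross-over only: "In case of patient cross-over, patients will be analyzed according to the intention-to-treat principle".

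**The concern.** Scores from the same wrist at 3 months, 1 year and 2 years will be correlated. When a later form does not come back, the earlier scores say something about what it would have shown. A test confined to one visit cannot use that information.

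Two things are at stake. The first is precision for the 1- and 2-year differences in a trial of 52 per group, followed by post in people aged 65 or more. The second is the missing-data assumption. A likelihood-based model over all visits remains valid when non-return depends on scores already observed. The unadjusted single-visit tests do not use those scores, so they can be biased if return depends on earlier function in a way that differs between the arms.

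The point concerns the estimator that the protocol names. It does not concern which time point is primary.

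**Working it through.** **Inputs from the protocol:** 52 per group, SD 14, target difference 11 (Power analysis); PRWE at three visits (Follow-up). The protocol gives no figure on this point to reproduce. Its sample-size arithmetic is a separate matter and is not used here.

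**Assumed, because the protocol gives none:** correlations (3 months-1 year, 3 months-2 years, 1-2 years) of 0.5/0.4/0.6, 0.6/0.5/0.7 or 0.7/0.6/0.8; the return rates below; monotone loss (once missing, always missing).

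**Formula.** Let n0, n1 and n2 be the numbers per group with PRWE at 3 months, 1 year and 2 years. A single-visit test has arm-mean variance SD²/n2. Under the repeated-measures model, in large samples, it is

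SD² × [(1 − R²)/n2 + (R² − r02²)/n1 + r02²/n0],

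with R² = (r02² + r12² − 2·r01·r02·r12)/(1 − r01²). The effective n is 1 divided by the bracket.

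**Worked case** (middle correlations; all seen at 3 months, 85% at 1 year, 70% at 2 years):

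- R² = (0.25 + 0.49 − 2 × 0.6 × 0.5 × 0.7)/(1 − 0.36) = 0.32/0.64 = 0.50.
- Bracket = 0.50/36.4 + 0.25/44.2 + 0.25/52 = 0.01374 + 0.00566 + 0.00481 = 0.0242.
- Effective n = 41.3 against 36.4, a gain of 13.5%.

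**All settings** (effective n per group at 2 years, gain in brackets):

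| Setting | n0 / n1 / n2 | Low corr. | Middle | High corr. |
|---|---|---|---|---|
| A: 30% missing, all after 3 months | 52 / 44.2 / 36.4 | 39.8 (9.4%) | 41.3 (13.5%) | 43.2 (18.8%) |
| B: 20% missing, all after 3 months | 52 / 46.8 / 41.6 | 44.1 (5.9%) | 45.1 (8.4%) | 46.4 (11.5%) |
| C: 30% missing, half before 3 months | 44.2 / 40.3 / 36.4 | 38.3 (5.1%) | 39.1 (7.3%) | 40.0 (10.0%) |
| D: 20% missing, half before 3 months | 46.8 / 44.2 / 41.6 | 42.9 (3.1%) | 43.4 (4.4%) | 44.1 (6.0%) |
| E: 30% missing, all before 3 months | 36.4 / 36.4 / 36.4 | 36.4 (0%) | 36.4 (0%) | 36.4 (0%) |

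Simulation of 8,000 trials per setting gave 8.6%, 13.4% and 17.9% for A, and 5.4%, 7.7% and 11.6% for B, close to the formula.

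**Cross-check with one earlier score,** complete in all 52, and correlation ρ with the 2-year score. The variance is SD²/52 × [ρ² + (1 − ρ²)/(1 − m)], where m is the fraction of 2-year forms missing. At m = 30%, ρ = 0.3, 0.5 and 0.7 give effective n of 37.4, 39.4 and 42.7 against 36.4. Power for 11 points, two-sided 5%, normal approximation, rises from 91.8% to 92.5%, 93.6% and 95.2%. At m = 20% it rises from 94.8% to 95.1%, 95.7% and 96.5%.

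**Interval width, setting A.** The standard error of the difference is 14 × √(2/n). It is 3.28 at n = 36.4, and 3.14 to 3.01 at n = 39.8 to 43.2. The 95% half-width (× 1.96) falls from 6.4 points to between 6.2 and 5.9.

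**Bias.** In simulation the true difference was −11 at both 3 months and 2 years, and non-return depended on the 3-month score. That left 29-31% missing in one arm and 19-22% in the other. Those who returned forms gave −10.8 to −10.1. Using the 3-month score gave about −11.0. The bias removed was between about 0.1 and 1.0 points.

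**The case against.** A per-visit comparison of randomised groups is a legitimate estimator, and the protocol contains no wrong number here. That is fair: this is a better choice among valid ones. It is still a choice that the protocol makes by naming its methods, so it can be improved there.

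A reader might infer several stronger things that the document does not support:

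- **That patients who miss a form are dropped and their scores wasted.** No deletion rule is stated, and a separate analysis plan may add a missing-data rule. A patient without a 2-year form still counts at 1 year, which is also part of the primary outcome, and at 3 months. The earlier scores are used at their own visits but do not inform the later one.
- **That the protocol itself expects 30% of forms to be missing.** Power analysis attributes its 30% to surgery during cast treatment. Patients lost then would have no PRWE at all, since the first is at 3 months, and no model recovers them (setting E). If they stay in follow-up as randomised, they are not missing. Neither reading gives a rate of unreturned forms.
- **That single-visit tests are unbiased only if return is unrelated to function.** If function and non-return follow the same pattern in both arms, the bias cancels in the difference. The planned regression also tolerates non-return explained by its covariates.

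A further objection stands in part: the protocol provides a rank test for skewed variables, and a normal-theory model is less comfortable for such scores. For PRWE the protocol already asserts normality, so a linear mixed model adds no new assumption about its shape. For the other scores the fix has to allow for skewness.

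**Conclusion.** The point holds as a matter of efficiency. Three readings per patient are collected, and every named method uses one visit at a time. For the 2-year comparison a repeated-measures model would add about 5-19% to the effective sample size in settings A to C, 3-6% in D, and nothing if all loss precedes 3 months. In the single-score check at 20-30% missing, that is 0.3 to 3.4 points of power. It also weakens the missing-data assumption, but the bias removed was under 1 PRWE point against a target difference of 11.

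All of this rests on assumed correlations, return rates and a missingness mechanism; the protocol supplies none. Correlations below those tried would shrink the gain. No conclusion of the trial is shown to depend on the change. It is worth making because the data are already planned.

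**What to change.** In Statistical analysis, make the main analysis of PRWE one likelihood-based repeated-measures model over 3 months, 1 year and 2 years, with:

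- cast, visit, cast × visit and the planned covariates;
- an unstructured within-patient covariance;
- the 1-year and 2-year cast differences reported from it with 95% confidence intervals.

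The 3-month PRWE enters as a response, not as a covariate, because it is measured after randomisation. Use the same model for QuickDASH, VAS and 15-D where residuals allow. Keep the single-visit t-test or Mann-Whitney test as a sensitivity analysis, including for skewed scores. Do not cite the 30% surgical allowance as the rate of unreturned forms.

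The cost is analysis wording only, with no new data or visits. The downside is a somewhat more complex model that relies on normal theory.
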